## Abstract

**Background:**

Nocturnal enuresis (NE), or ‘bedwetting’, is a form of night-time urinary incontinence occurring in younger children. A diagnosis of NE can be socially disruptive and psychologically stressful for a child. The most common strategies used by parents to manage NE are waking the child during the night to use the bathroom and limiting the child’s water intake before going to bed. Behavioural or educational therapies for NE such as urotherapy or bladder retraining are widely accepted and considered as a mainstream treatment option for non-neurogenic lower urinary tract dysfunction in children. Pharmacotherapy also plays an ancillary role. However, there is no gold standard therapy or intervention to effectively manage NE.

**Methods:**

This study aims to determine the efficacy of a herbal combination in the treatment of NE in children. The target population for this study is 80 children aged between 6 and 14 years old (males and females) who have primary nocturnal enuresis ≥3 per week (wet nights). The active group will receive one or two capsules per day containing 420 mg of a proprietary blend of Urox® (Seipel Group, Brisbane, Australia) containing Cratevox™ (*Crataeva nurvala* L; Capparidaceae; Varuna) stem bark extract standardised for 1.5% lupeol: non-standardised *Equisetum arvense* L. (Equisetaceae; Horsetail) stem extract; and, non-standardised *Lindera aggregata* Sims. The primary outcome for this study is the frequency of nocturia. Secondary outcomes include safety, quality of life, and daytime incontinence. Each participation will be involved in the trial for 32 weeks including contact with the research team every 2 weeks for the first 8 weeks and then every 8 weeks until trial completion.

**Discussion:**

This study examines a novel treatment for an under-researched health condition affecting many children. Despite the availability of several therapies for NE, there is insufficient evidence to support the use of any one intervention and as such this randomised placebo-controlled phase II trial will be an important contribution to understanding potential new treatments for this condition.

**Trial registration:**

Australian and New Zealand Clinical Trials Registration Number: 12618000288224.

Protocol: 23 February 2018, version 1.1.

## Background

Nocturnal enuresis (NE), or ‘bedwetting’, is a form of night time urinary incontinence occurring in younger children [1, 2]. More specifically, primary nocturnal enuresis (PNE) is defined as the involuntary discharge of urine at night in children aged 5 years or older, who do not have congenital or acquired defects of the central nervous system or urinary tract and have not experienced a dry period of more than 6 months [1]. NE is classified as either *monosymptomatic enuresis* – enuresis with no other lower urinary tract symptoms – or *non-monosymptomatic enuresis* – enuresis with other, mainly daytime, lower urinary tract symptoms [3]. The aetiology of NE has been attributed to multifactorial pathophysiological factors such as an altered antidiuretic hormone profile with nocturnal polyuria, arousal failure, delayed bladder maturation and nocturnal detrusor overactivity [4, 5]. Common co-morbidities identified with NE are: constipation, diabetes mellitus, developmental attention or learning difficulties, history of recurrent urinary tract infection (UTI) in boys, and pinworm infestation [6–8]. Current NE international prevalence rates are reported as between 5 and 20% of children over 5 years old [4, 7, 9–11] with an incidence as high as 18.2% in an Australian school-aged children cohort. Predictive or risk factors which have been linked with NE include: age, male gender, daytime incontinence, encopresis, social concerns, delayed age of walking, positive parental history of enuresis, and sibling history of enuresis [7, 9, 12].

A diagnosis of NE can be socially disruptive and psychologically stressful for a child [2, 10]. Quality of life indicators have been explored in the past to determine the impact of NE on the life of children [9, 13, 14]. The psychological impact of bladder dysfunction has been understood to be due to the urinary symptoms themselves [13]. Though not a causal factor, poor school performance has been reported to be higher in children with NE [9]. A child’s interpretation of the impact of NE on their own life also appears to vary from the parental proxy perception of quality of life [13, 15]. Parents have reported more often (71%) that NE had little or no impact on their child’s overall quality of life, as they believed it was a developmental condition [9]. This is supported by the fact that only half the amount of parents consult a medical practitioner for this condition [16], which suggests that the prevalence could be higher in the community than indicated by current documented Figures [17].

### Common approaches to treatment for nocturnal enuresis

Parents often choose a combination of therapies to treat their children with NE. The most common strategies utilised are waking the child during the night to use the bathroom and limiting the child’s water intake before going to bed [18]. Behavioural or educational therapies for NE such as urotherapy or bladder retraining are widely accepted and considered as a mainstream treatment option for non-neurogenic lower urinary tract dysfunction in children [19] with the aim to normalise bladder emptying and storage by teaching relaxed voiding techniques [20]. Alarm interventions have demonstrated moderate effectiveness in reducing NE in approximately two thirds of children with relapse occurring in half children with ceasing the treatment [21]. Transcutaneous electrical nerve stimulation (TENS) has been examined for the treatment of NE, but has mixed efficacy, with reported benefit in reducing NE events in children with primary NE [22] yet no effect on children with monosymptomatic NE [23].

Pharmacotherapy plays an ancillary role with generally accepted pharmacological treatment options such as desmopressin, tricyclics, or anticholinergics administered orally [6]. Though much research has focussed on using pharmacotherapy to treat NE, only a minority of children actually receive such medication (9.1%) [18]. Most children prescribed medications such as tricyclics and desmopressin have shown improvement in reducing the number of wet nights but have been shown to relapse after stopping active treatment [21]. Parents have also demonstrated low compliance (17.2%) in persisting with medication for their children with NE [18].

The adverse effects of desmopressin are dose related [24] with most reactions related to study medication manifesting as drug hypersensitivity symptoms such as; abdominal pain, headache, nausea, flushing face, and asthma-related symptoms. An integrative approach to treatment has been suggested in the past, given the multifactorial nature of NE, issues of pharmacotherapy treatment refractoriness, and considerations to risk/benefit in treatments [1]. NE has the potential to significantly impact the psychological and social wellbeing of a child, thus alternative treatment options that could be administered with reduced adverse effects need to be explored. However, without an established standard treatment with strong evidence effectiveness, new treatments should be examined through placebo-controlled studies [25].

### Herbal medicine for nocturnal enuresis

Given that prescription medications are cautiously used in children and potentially have undesirable side effect profiles, controlled clinical trials are needed to explore complementary medicine (CM) treatments such as herbal medicine for safety and efficacy. A Cochrane review on complementary medicine and miscellaneous interventions for NE was published in 2011 and highlighted the need for larger and more rigorous trials examining CM treatment options [10]. The review concluded that although the outcome measures varied, herbal medicine seemed to perform better than imipramine, both during and after treatment [10].

Herbal medicine has traditionally been used in the treatment of symptoms for NE or urinary incontinence [10, 11]. A historical account by Glicklich [26] chronicles the use of herbal medicine to treat children with enuresis from as early as the time of the Papyrus Ebers dated 1550 B.C. In contemporary society, parents of children with NE frequently seek herbal products from pharmacists to treat this condition, which has led to an increased consumer demand and an associated increased availability in pharmacies [27]. Prior and emerging clinical research into the use of herbal medicine continues to show promising outcomes and increased benefits in reducing the relapse of symptoms in NE [28, 29]. Early herbal medicine research for the treatment of NE has mainly utilised herbs drawn from Traditional Chinese medicine practices [1, 11].

### UROX® and adult urinary incontinence

Urox® is an herbal formulation listed with the Australian Therapeutic Goods Administration which contains a combination of *Crateva nurvala*, *Equisetum arvense* and *Lindera aggregate* (see Fig. 1). Urox® has been trialled previously in a phase 2, randomised, double-blind placebo controlled trial to reduce the symptoms of overactive bladder (OAB) and urinary incontinence (UI) in adults (NCT02396160) [30]. One hundred and fifty patients were randomised to receive active or placebo capsules for 8 weeks. The primary outcome measure was urinary frequency defined as the number of voluntary diurnal and / or nocturnal micturition, self-reported via a validated urinary diary. Secondary outcomes included the common urinary symptoms of; urinary frequency, nocturia, urgency and stress incontinence using participant micturition diaries. Further secondary outcomes included health-related quality of life measurements using validated questionnaires, the incontinence impact questionnaire (IIQ) and the urinary distress inventory (UDI) [30].

**Fig. 1 Fig1:**

Summary of formulation information

The study determined that there was a reduction in all urinary symptoms (i.e. day frequency, nocturia, urgency, urgency incontinence, stress incontinence and total incontinence) which reached statistical significance in all parameters. Specifically, day frequency (n/day) reduced from 11.53 ± .54 to 7.69 ± 2.15, statistically significant when treatment and placebo groups were compared (*p* = 0.01, 0.01–0.02). The frequency of nocturia (n/day) was also notably reduced 4.02 ± 1.62 to 2.16 ± 1.49 after 8 weeks of treatment. The treatment vs placebo at 8 weeks was statistically and clinically significant (*p* = 0.03, 0.02–0.05). Urinary urgency (OR 0.02; 95%CI 0.01 to 0.03), and total incontinence (OR 0.03; 95% CI 0.01 to 0.06) were also lower (all *p* < 0.01) in the treatment group. Quality of life was also noted to be significantly improved after treatment in comparison to placebo utilising [30].

## Methods/design

### Objectives

#### Aim

The aim of the study is to determine the efficacy of the combination of *Crateva nurvala*, *Equisetum arvense* and *Lindera aggregata* in the treatment of nocturnal enuresis in children, as assessed by frequency of nocturnal enuresis.

#### Hypothesis

The combination capsule of the herbal formula ‘Urox- Bedtime Buddy’ will reduce the frequency of nocturnal enuresis in children aged 6 to 14 years.

#### Objectives

To improve the quality of life for children that experience bed wetting issues by reducing the number of times the child wets the bed a week.To reduce the frequency of bed wetting a child experiences a week which has the potential to improve their physical, psychological and social wellbeing.

##### Trial design

This is a randomised, prospective, double-blind randomised, placebo-controlled trial in which participants, researchers and statisticians analysing the data are blinded to which group the participants are randomised. It is a parallel group or non-crossover study. The allocation ratio is 1:1.

### Methods: participants, interventions, and outcomes

#### Study setting

The research setting is Endeavour College of Natural Health, [name] in Brisbane. There is a site agreement between UTS and Endeavour College of Natural Health, Brisbane Campus.

#### Eligibility criteria

The target population for this study is children aged between 6 and 14 years old (males and females) who have primary nocturnal enuresis ≥3 per week (wet nights). Potential participants will be excluded if they report a diagnosis of vesicoureteral reflux, spinal dysraphism, recent urotherapy, recent or current urinary tract infection (< 1 week), active cancer with current treatment, a history of cardiac failure and a history of renal disease or urinary retention.

#### Interventions

##### Active intervention

Each capsule contains 420 mg of a proprietary blend of Urox® (Seipel Group, Brisbane, Australia) containing Cratevox™ (*Crataeva nurvala* L; Capparidaceae; Varuna) stem bark extract standardised for 1.5% lupeol: non-standardised *Equisetum arvense* L. (Equisetaceae; Horsetail) stem extract; and, non-standardised *Lindera aggregata* Sims. The TGA Approval number for the product is – AUSTL 194355. Capsules were manufactured in a Therapeutic Goods Administration licensed facility according to the PIC/S Guide to Good Manufacturing Practice for Medicinal Products, PE 009–9-15 January 2009. Capsules were subjected to microbiological and heavy metal testing to ensure they complied with product specifications.

The adult dose is two capsules per day taken once daily with food. The dosage is 1 capsule in the morning (< 40 kg) or 2 capsules in the morning (> 40 kg) for children. The dosage regimen was determined based on several integral methods as follows; earlier research with *Crataeva* and *Equisetum* alone [31, 32] and more recently with Schoendorfer, et al’s trial [30] with Urox which includes the newer formulation with 3 ingredients; pharmacopeia and traditional herbal medicine textbook dosage recommendations [33, 34] and Clark’s rule for dosage in Children (Dose = Adult dose x Weight(kg) / 70) which is conservative and tends to underestimate the required dose [35]. Urox was listed on the ARTG 6th February, 2012 and was marketed in Australia from this date. The Bedtime Buddy is the same formula as Urox but dosed for children and was listed with the TGA on the 14th June, 2017 – AUSTL 290162.

##### Placebo

The active intervention will be compared with an identical vegetarian capsule containing colour-matched cellulose to that of the active ingredient. Participants will be prescribed 1 capsule in the morning (< 40 kg) or 2 capsules in the morning (> 40 kg).

#### Outcomes

##### Primary outcome

**Frequency of nocturnal enuresis (Week 8)**

The primary outcome for this study will measure efficacy as quantified by the change from baseline in the frequency of nocturnal enuresis at week 8. Parents are completing a daily diary (see Fig. 3) online or via hard copy which measures episodes of nocturia (waking wet through the night, and / or waking wet in the morning). The diary also captures the volume of fluid consumed in the day, together with the compliance of taking the capsule each day.

##### Secondary outcomes

**Frequency of nocturnal enuresis (Week 4 and Week 32)**

In addition to the primary outcome, change from baseline in the frequency of nocturnal enuresis at week 4 and Week 32 will also be measured.

**Safety (Week 4 and Week 8)**

Secondary outcomes in Stage 1 will include on the safety of the herbal formulation in children aged 6–14 years at Weeks 4 and 8 of the study. Data will be collected from adverse reactions (type, severity, relation to investigational product), and side effects experienced by the participant recorded in the diary. An interim analysis will be conducted after enrolment of 30 participants to assess safety and continuation of the trial. Also at this time point, a power calculation to confirm participant numbers needed to reach statistical significance will determine the total number of participants required for recruitment. Safety data will be continued to be collected throughout Stage 2.

**Quality of Life (Week 4, Week and Week 32)**

Further secondary outcomes will measure health-related quality of life as measured by the Paediatric quality-of-life questionnaire (PinQ). This is a well-validated tool that measures the impact of NE on paediatric quality of life [13]. Permission has been granted by the author to use in this trial [36]. The PinQ will be completed by parent and child on separate data collection forms as it has been shown that there has been inconsistencies in proxy and child answers when filling in the questionnaire [13]. If a child is unable to complete a questionnaire due to lack of cognitive or communicative development, the researcher will assist the child in developmentally appropriate language to complete the questions. The PinQ will be completed at Baseline, Week 4, Week 8 and Week 32. Change in Quality of Life will be calculated based on difference from baseline at Week 4, Week 8 and Week 32.

**Daytime incontinence symptoms (Week 4, Week 8 and Week 32)**

There is a possibility that the capsule will impact on day-time symptoms of incontinence in children as this was demonstrated in an adult clinical trial with the same formulation [30]. These symptoms are measured at baseline, Week 4, Week 8 (in clinic visits) and Week 16 and Week 24 (over the phone), and in the final visit at Week 32. Data collection will note if there has been episodes of day-time urinary incontinence, urgency, constipation, faecal incontinence. If the parent answers yes to any of the above categories, they average how many times per week it has occurred for each symptom. Change in daytime incontinence symptoms will measured as difference from baseline at week 8 and week 32.

**Total response to treatment (Week 4, Week 8 and Week 32)**

Response to treatment will also be calculated based on the International Children’s Continence Society guidelines [37]. Less than 50% reduction in wet nights will be defined as ‘no response’, 50–99% reduction in wet nights will be considered a ‘partial response’. Participants will only be defined as having a ‘response’ if a 100% reduction in wet nights is reported. This will be calculated based on difference from baseline at Weeks 4, 8 and 32.

#### Trial duration

Each participation will be involved in the trial for 32 weeks. The overall flow of study involvement is reported in Fig. 2. The first 8 weeks involve the oral ingestion of the daily capsule. The post-interventional period involves weekly entry in the electronic diary recording any ongoing episodes of nocturia for 6 months to determine the long-term effects of the capsule on NE. There is also 2 monthly follow up phone calls to the note any new changes to medications or additional NE treatments as well as the daytime continence questions. A final visit to the clinic will occur at Week 32.

**Fig. 2 Fig2:**
[figure not shown]
CONSORT flow chart

#### Sample size

To detect a difference between the intervention group and the control group, a calculation from a trial on desmopressin and oxybutynin [38] was conducted. The power calculation used 80% power for 5% significance based on three-month results (*p* = 0.001). This resulted in the number of children required to recruit being 80 participants. This allows for a 20% attrition rate which provides an adequate number of participants in the primary analysis.

Due to the absence of existing studies involving similar populations and interventions, an interim sample size calculation will be conducted to confirm and potentially readjust the sample size as appropriate. The recalculation of the sample size will be conducted after 30 participants have completed the trial. The difference in the change (from baseline) in the frequency of nocturnal enuresis at week 8 will be calculated. This difference will then be imputed into the same equation used for the sample size calculation applied during study design. Any readjustment on the trial recruitment numbers will be resubmitted to the authorising HREC committee with the interim sample size calculation.

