#### Statistical methods

All data will be analysed on STATA©14. Analyses will be conducted on an intention to treat basis. Descriptive and inferential statistics will be conducted. The difference in change between groups will be analysed using paired T-tests and Analysis of Variance (ANOVA). Groups will be compared at baseline and if difference(s) is/are ascertained, the variable(s) will be entered into the regression model to appropriately adjust the analyses. Sensitivity analyses will also be conducted to account for incomplete adherence to protocol. Interim statistical analysis for safety will occur after 30 participants have completed. This is same timing as the re-evaluation of the sample size calculation. All baseline, demographic, safety and efficacy outputs data will be summarised by treatment group. In summary tables of continuous variables, the minimum and maximum statistics the arithmetic mean and median, the 95% confidence interval, standard deviation, and standard error will be presented to the same number of decimal places as the original data. Safety outputs will be documented at the interim analysis and end of trial in columns with number, severity, treatment group and percentage. All hypothesis testing will be carried out at the 5% (2-sided) significance level unless otherwise specified. *P* values will be rounded to three decimal places. *P* values less than 0.001 will be reported as < 0.001 in tables (Table 1).

**Table 1 Tab1:** Details of the active and control interventions

Arms	Assigned Interventions
Active Comparator: Treatment 1 capsule in the morning (≤40 kg) or 2 capsules in the morning (> 40 kg) for 8 weeks duration.	Dietary supplement: Bedtime Buddy Active treatment- Proprietary combination of 420 mg of herbs. expressed as dry herb equivalent: Crateva nurvala 3000 mg (120 mg) *Equisetum arvense* 1500 mg (150 mg) Lindera Aggregata 1500 mg (150 mg)
Control Comparator: Placebo 1 capsule in the morning (≤40 kg) or 2 capsules in the morning (> 40 kg) for 8 weeks duration.	Placebo- Identical vegetarian capsule containing colour-matched cellulose to that of the active treatment

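### The 80% power claim for 80 children is not tied to the week-8 endpoint, and the planned recalculation cannot repair it because it uses the observed difference from about 30 children

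*Protocol article*

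**What the plan says.** In the protocol article, the Sample size section bases the calculation on "a calculation from a trial on desmopressin and oxybutynin" and continues: "The power calculation used 80% power for 5% significance based on three-month results". The one result reported from that trial is p = 0.001. The section then says: "This resulted in the number of children required to recruit being 80 participants". On dropout it adds: "This allows for a 20% attrition rate which provides an adequate number of participants in the primary analysis".

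The Primary outcome section defines the endpoint as the "change from baseline in the frequency of nocturnal enuresis at week 8". The capsule is taken for 8 weeks and compared with placebo at 1:1 allocation. The Statistical methods section sets the test level: "All hypothesis testing will be carried out at the 5% (2-sided) significance level unless otherwise specified".

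The Sample size section also acknowledges that no studies exist in a similar population with a similar intervention, and for that reason plans a recalculation after 30 participants. The observed between-group difference in week-8 change is to be put into the equation used at the design stage, and any new target goes to the ethics committee. The Monitoring section repeats the plan and says that the person doing the interim analysis is blinded to allocation.

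**The concern.** A power statement means something only for a stated difference and SD on the endpoint to be tested. Here 80% power is claimed without qualification. Its stated basis is a trial of other drugs, read at three months, while this trial tests a herbal capsule against placebo at week 8. The single result quoted is a p-value, which combines effect and sample size and does not by itself say what difference was planned for. A reader cannot tell what size of benefit a null result would make unlikely.

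The recalculation is meant to cover this gap, and it does use the right endpoint and comparison. But it takes as its input the difference observed in about 30 children. That difference is very imprecise, and the required sample size depends on its inverse square, so the new target would follow chance more than information. The target sent to the ethics committee would rest on that figure.

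**Working it through.** **Inputs from the protocol article.** Total 80, attrition 20%, power 80% (Sample size); 1:1 allocation (Trial design); 5% two-sided (Statistical methods); change from baseline at week 8, treated as continuous (Primary outcome). Difference, SD and response rates: none stated.

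**1. The plan's own figure.** The 80 cannot be derived from the stated inputs, because no effect size is given. Only the attrition step can be checked: 64 / (1 − 0.20) = 80, so 80 × 0.8 = 64 evaluable children, 32 per arm. That step is consistent.

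**2. What 32 per arm can detect.** Normal approximation: d = (1.96 + 0.84) × √(2/32) = 2.80 × 0.25 = 0.70 SD. The two-sample t-test gives 0.711 SD. If all 80 children were evaluable (40 per arm), the t-test gives 0.634 SD.

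Power of the t-test with 32 per arm:

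| True difference (SD) | Power |
|---|---|
| 0.6 | 66% |
| 0.5 | 50% |
| 0.4 | 35% |
| 0.3 | 22% |

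**3. Precision of the interim difference.** With about 15 per arm, the standard error in SD units is √(2/15) = 0.365, or about 0.37 SD. A 95% interval is about ±0.72 SD, as wide on each side as the 0.71 SD that the trial can detect.

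**4. What the recalculation would ask for.** Total evaluable N = 4 × (2.80)² / d² ≈ 31.4 / d². The design equation is not printed, so I assume this standard formula.

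| Assumed true effect | Observed d, one SE above | N | Observed d, one SE below | N |
|---|---|---|---|---|
| 0.50 SD | 0.865 | 31.4 / 0.748 ≈ 42 | 0.135 | 31.4 / 0.0182 ≈ 1,700 |
| 0.71 SD | 1.075 | 31.4 / 1.156 ≈ 27 | 0.345 | 31.4 / 0.119 ≈ 264 |

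For comparison, 0.5 SD itself needs 31.4 / 0.25 ≈ 126 evaluable children. About one interim in three would fall outside even these one-standard-error limits.

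**The case against.** A reader might infer that the p-value itself was fed into the power formula, or that the trial does not have 80% power. The document supports neither. The calculation is said to be based on the three-month results, with p = 0.001 added in brackets to describe them. The recalculation puts a difference into the same equation, which suggests that the design stage also used a difference, simply not printed. A journal article may leave such detail to the full protocol, so unprinted inputs alone would not be a finding.

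The p-value does not refute 80 either. The source trial's size is not given. If one assumes a two-arm 1:1 source, p = 0.001 corresponds to 2 × 3.29 / √n: 1.04 SD with 40 patients, 0.47 SD with 200, and about 0.70 SD with 86 to 88, which is close to what 64 evaluable children can detect. Nothing in the article shows that 0.3 to 0.5 SD is more realistic than 0.71 SD, and the regression adjustment foreseen under Statistical methods could lower the detectable difference. All of this stands.

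It can also be said that the borrowed evidence is disclosed and that the recalculation uses this trial's own week-8 data. That is true of the endpoint. It does not answer the imprecision of the number entered. It also leaves in place that the basis the article does state concerns other drugs and another time point.

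**Conclusion.** The point holds in a limited form. The 80% power claim cannot be tied to the week-8 comparison of herbal capsule and placebo: its stated basis is a different treatment at three months, and no week-8 difference or SD is stated. What can be said is that 64 evaluable children give 80% power for 0.71 SD and about 50% for 0.5 SD. Whether the trial is underpowered is open.

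The more consequential defect is the recalculation rule. With a standard error of about 0.37 SD, an interim one standard error either side of a true 0.5 SD asks for roughly 40 to 1,700 evaluable children.

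These figures assume an unadjusted two-group comparison, equal SDs, 20% attrition, about 15 children per arm at the interim and the standard two-means formula. Full retention would bring 0.71 down to 0.63 SD.

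**What to change.** Keep 80 and replace the reference to p = 0.001 and the three-month results with wording such as: *64 evaluable children (32 per arm) give 80% power, two-sided 5%, for an unadjusted between-arm difference of 0.71 SD in change in wet nights per week at week 8, and about 50% power for 0.5 SD.*

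State the planning difference in wet nights per week, with its assumed SD, and justify it as a difference worth detecting. It should not simply be 0.71 SD worked back from 80.

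In the recalculation, hold that difference fixed. Update only the SD, pooled over both arms without unblinding, and the attrition rate. Do not enter the observed interim difference. This also suits the Monitoring section's statement that the interim analyst is blinded.

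Cost: no additional children at the design stage. The stated power becomes less favourable, and the recalculation no longer responds to the observed effect.
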